## Abstract

**Background:**

Dietary behaviour interventions have the potential to reduce diet-related disease. Ample opportunity exists to implement these interventions in the workplace. The overall aim is to assess the effectiveness and cost-effectiveness of complex dietary interventions focused on environmental dietary modification alone or in combination with nutrition education in large manufacturing workplace settings.

**Methods/design:**

A clustered controlled trial involving four large multinational manufacturing workplaces in Cork will be conducted. The complex intervention design has been developed using the Medical Research Council’s framework and the National Institute for Health and Clinical Excellence (NICE) guidelines and will be reported using the TREND statement for the transparent reporting of evaluations with non-randomized designs. It will draw on a soft paternalistic “nudge” theoretical perspective. Nutrition education will include three elements: group presentations, individual nutrition consultations and detailed nutrition information. Environmental dietary modification will consist of five elements: (a) restriction of fat, saturated fat, sugar and salt, (b) increase in fibre, fruit and vegetables, (c) price discounts for whole fresh fruit, (d) strategic positioning of healthier alternatives and (e) portion size control. No intervention will be offered in workplace A (control). Workplace B will receive nutrition education. Workplace C will receive nutrition education and environmental dietary modification. Workplace D will receive environmental dietary modification alone. A total of 448 participants aged 18 to 64 years will be selected randomly. All permanent, full-time employees, purchasing at least one main meal in the workplace daily, will be eligible. Changes in dietary behaviours, nutrition knowledge, health status with measurements obtained at baseline and at intervals of 3 to 4 months, 7 to 9 months and 13 to 16 months will be recorded. A process evaluation and cost-effectiveness economic evaluation will be undertaken.

**Discussion:**

A 'Food Choice at Work’ toolbox (concise teaching kit to replicate the intervention) will be developed to inform and guide future researchers, workplace stakeholders, policy makers and the food industry.

**Trial registration:**

Current Controlled Trials, ISRCTN35108237

## Background

Altering people’s health-related behaviours can have a substantial impact on the main causes of mortality and morbidity [1]. Behavioural interventions can modify current patterns of disease [1]. Diet-related disease is a major public health concern and continues to endanger our population health and the sustainability of our healthcare systems [2]. Dietary intake of fat (especially saturated fat and trans fat), sugar and salt play a critical role in the development of hypertension, obesity, type 2 diabetes and cardiovascular disease [3].

Dietary behaviour is influenced by a complex net of individual, environmental, societal, biological and psychological factors [4,5]. Given the complicated intricacies of dietary behaviour, there is a need to develop effective complex behavioural interventions to promote dietary change in the population. Complex interventions have several interacting components and should be developed systematically with appropriate evidence and theory [1,6]. These interventions should be piloted carefully and the process of implementation should be monitored [6].

The workplace is an ideal setting to implement these complex interventions, as most adults spend approximately 60% of their waking hours at work [7]. The workplace environment is a microcosm of society [8]. It is the most appropriate setting to examine complex dietary interventions as it can tolerate the interacting components of these interventions while assessing the impact in relatively homogenous workplace populations in controlled environments [8]. Relevant reviews agree that these interventions may be more effective if they are of high intensity, developed within a complex framework and comply with a robust study design [5,8-12].

However, there are substantial gaps in the current evidence base [8-13]. Although a moderate positive effect on dietary behaviour has been reported, particularly with fruit and vegetable intakes [9-12], workplace dietary intervention studies to date are of low-intensity with suboptimal study designs [9-13]. These interventions focus on information provision and fail to examine environmental approaches, such as food modification and real incentives, for example, price discounts [8]. Inconsistent reporting of previous studies has also precluded meta-analysis. Therefore, the impact of complex workplace dietary behaviour interventions is still unknown.

The aim of this study is to assess the effectiveness and cost-effectiveness of complex dietary interventions focused on environmental dietary modification alone or in combination with nutrition education in large manufacturing workplace settings. The study design is informed by the findings of a systematic review conducted by the authors [14].

This high-intensity complex intervention design is guided by appropriate structured frameworks and guidelines, including those of the Medical Research Council [6] and the National Institute for Health and Clinical Excellence (NICE) [1]. This study will be reported according to the TREND statement [6,15].

Environmental dietary modification and nutrition education approaches in this study will primarily draw on a soft paternalistic 'nudge’ theoretical perspective [16]. As recommended by the World Health Organization, catering and workplace stakeholders, including employees, will actively develop aspects of the intervention with the research team according to the specific characteristics of the included workplaces [4].

A process evaluation will be conducted. A cost-effectiveness economic evaluation will be undertaken in each workplace following a previous framework developed by Drummond *et al*. [17]. Very few studies have used cost-effective techniques to evaluate workplace interventions. Recently, Sacks *et al*. found that the traffic-light nutrition labelling offered excellent value for money as an obesity-prevention measure [18]. Absenteeism trends will also be monitored before and after the intervention to measure differences in labour productivity.

### Study hypothesis

Workplace complex dietary interventions that combine environmental dietary modification and nutrition education are more effective and cost-effective than nutrition education interventions alone or environmental dietary modification interventions alone when considering positive changes in dietary behaviour, health status and diet-related disease risk.

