#### Determination of sample size

A decrease in BMI by 1 kg/m^2^ (1 unit) and a 2 g average fall in dietary salt intake would have population health significance and clinical significance in terms of the risk of diet-related disease, for example, hypertension. To detect this difference in BMI between the control and intervention groups at follow-up session after 7 to 9 and 13 to 16 months and assuming a common standard deviation of 3.77, it is estimated that a sample size of 448 (112 per workplace) would have 80% power at the 5% significance level (findings from a previous study show that a 1 kg/m^2^ difference was independently associated with 13% higher risk for hypertension) [25,26]. The study will also be adequately powered (80% power at the 5% significance level) to detect a fall in dietary salt intake between the control and intervention groups at follow-up periods of 7 to 9 and 13 to 16 months using a standard deviation of 4.2 (In a previous intervention study the response within each participant group was normally distributed with standard deviation 4.2) [27].

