##### Statistical analysis

Data will be recorded manually and entered electronically into a Stata statistical software package prior to statistical analysis. Data manipulation and statistical analyses will be conducted using Stata. Primary analysis will examine the effects of the interventions by measuring changes in dietary behaviour, health status outcomes and nutrition knowledge.

Data regarding individual and environmental factors that may influence the effectiveness of the dietary complex interventions will be collected during baseline and follow-up. Individual factors will include personal (age, sex, ethnicity, education status, nutrition knowledge), lifestyle (smoking status, alcohol consumption, physical activity) and workplace factors (shift-work patterns, work status, for example, production worker, work schedule). Environmental factors will include the employees (sex breakdown and age profile) and the workplace structure (number of employees in workplace, canteen arrangement, for example, opening hours, employee structure, for example, percentage of employees working in production).

Proportions in workplaces A, B, C and D will be compared using Pearson’s chi-square and McNemar’s test for paired data. Mean levels of macronutrients, fibre, salt, fruit and vegetable intake in workplaces A, B, C and D will be compared and analyzed using a repeated measure analysis of variance (ANOVA) model. To measure nutrition knowledge, all participant responses to the GNKQ will be coded numerically and converted to a corrected score, as defined by Parmenter and Wardle [22].

A mixed effects model will examine subject variation in the longitudinal trends in dietary behaviour, explore associations between trends in dietary behaviour and health status over time in workplaces A, B, C and D and adjust for the potential confounding effect of other factors such as age, sex and shift-work patterns. The cost-effectiveness economic evaluation will be completed using a similar framework to Drummond *et al*. [17] and Roberts *et al*. [39].

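### The sample size is justified for control versus intervention, not for the C–B and C–D comparisons that make up the study hypothesis, and the stated analyses do not single these out

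*Protocol article*

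**What the plan says.** **Protocol article, Study hypothesis.** Combined interventions "are more effective and cost-effective than nutrition education interventions alone or environmental dietary modification interventions alone". Under Modelling process and outcomes, workplace A is the control, B receives education, C receives both components and D receives environmental modification. The hypothesis is therefore about C–B and C–D; the control is not mentioned in it.

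**Protocol article, Determination of sample size.** The BMI calculation is made "To detect this difference in BMI between the control and intervention groups at follow-up session after 7 to 9 and 13 to 16 months", with a 1 kg/m² difference and "assuming a common standard deviation of 3.77", giving 448 in total, 112 per workplace, for 80% power at the 5% level. The salt statement has the same form and the same two visits (in months): "to detect a fall in dietary salt intake between the control and intervention groups at follow-up periods of 7 to 9 and 13 to 16". Its SD is given separately: "using a standard deviation of 4.2". The salt effect comes from the preceding statement that "a 2 g average fall in dietary salt intake would have population health significance and clinical significance".

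**Protocol article, Statistical analysis.** Proportions in the four workplaces are compared by chi-square and McNemar tests. Mean intakes "will be compared and analyzed using a repeated measure analysis of variance (ANOVA) model". A mixed effects model covers trends over time in all four. No pairwise contrast is picked out.

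**Elsewhere.** The aim and objective 1 concern the effect of the interventions. Objective 4 compares the alternatives on costs and consequences, and the economic evaluation plans incremental cost-effectiveness ratios for each alternative.

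**The concern.** The comparison that is hypothesised and the comparison that is powered are different. A difference among four workplaces can arise only because A differs from the rest. C better than A can arise when C is no better than B or D. Neither result bears out the hypothesis, but the text does not say which result would.

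The difference also matters for size. By identity, C–B = (C–A) – (B–A). If education alone has any benefit, C's advantage over B is smaller than its advantage over A; the same holds for D. An effect chosen as worthwhile against no intervention is therefore a generous target for the increment over an active component. At stake is whether a favourable comparison with A is reported as confirming that combining the components is better, and whether readers take the stated 80% to cover that claim.

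**Working it through.** **Inputs.** From Determination of sample size: BMI difference 1 kg/m², SD 3.77; salt difference 2 g, SD 4.2; 112 per workplace; 80% power; 5% level. Two-sided testing is assumed, and it reproduces the stated total. No allowance for clustering or dropout is stated there and none is made here.

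**1. The plan's own figure.** For two equal groups, n per group = 2·SD²·(1.960 + 0.842)²/d² = 2 × 3.77² × 7.849 / 1² = 223.1, so 224. Two groups give 2 × 224 = 448, which is the stated total. It reproduces as a comparison of 224 with 224, not of 112 with 112.

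**2. BMI, C–B or C–D at 112 against 112.** SE = 3.77 × √(2/112) = 0.504. For 1 kg/m², 1/0.504 = 1.985, and power = Φ(1.985 – 1.960) = Φ(0.025) = 0.51. The difference detectable with 80% power is 0.504 × 2.802 = 1.41 kg/m². Having 80% power for each contrast at 1 kg/m² would take 224 per workplace, 896 in all.

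**3. BMI, both contrasts.** The two contrasts share arm C, so with equal arms their correlation is 0.5. The bivariate normal probability that both exceed 1.960 is 0.34 when the true difference is 1 kg/m² in each.

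**4. Smaller increments (assumed; the article gives no C–B or C–D difference).**

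| True BMI difference | Each contrast | Both |
|---|---|---|
| 1 kg/m² | 51% | 34% |
| 0.75 kg/m² | 32% | 17% |
| 0.5 kg/m² | 17% | 7% |

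**5. How much belongs to the mismatch.** C–A is also 112 against 112, so it too has 51% power at 1 kg/m². Even A (112) against all intervention workplaces pooled (336) gives SE = 3.77 × √(1/112 + 1/336) = 0.411 and power Φ(2.431 – 1.960) = 0.68. The fall from 80% to 51% is therefore due to spreading 448 over four workplaces. The further fall down the table in step 4 is what follows from the hypothesised contrasts being smaller than contrasts with A.

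**6. Salt.** SE = 4.2 × √(2/112) = 0.561. At 2 g, power = Φ(3.563 – 1.960) = 0.95 for each contrast; at an assumed 1 g, Φ(1.782 – 1.960) = 0.43. The detectable difference is 0.561 × 2.802 = 1.57 g.

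**7. Sensitivity to analysing change from baseline.** The SD of change is SD × √(2(1 – r)), where r, the correlation of baseline with follow-up, is not given. If 3.77 is the SD at a single visit, r = 0.5 leaves it at 3.77, and step 4 stands. An assumed r = 0.8 gives 3.77 × √0.4 = 2.38. Power is then 88% for each contrast and 80% for both at 1 kg/m², and 35% and about 19% at 0.5 kg/m².

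**The case against.** A reader might infer that the trial does not test its own hypothesis at all. The article does not support that. All four workplaces enter every planned comparison, so C–B and C–D can be estimated from the stated models. Objective 4 and the incremental cost-effectiveness ratios compare the alternatives directly, which serves the cost-effectiveness half of the hypothesis.

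It can also be said that listing contrasts is detail that an article leaves to an analysis plan. That is fair, and the lack of named contrasts would not be a finding alone. What remains is a mismatch between two things the article does state: its hypothesis and the comparison used to justify its sample size. An analysis plan cannot make that 80% apply to a different comparison.

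The 51% should not be blamed wholly on the mismatch, since C–A has the same figure. Nor is the trial short of power for the hypothesis on every outcome: at the article's own 2 g, salt has about 95% per contrast. With a highly correlated baseline, BMI could also do much better than 51%, though only under an assumed correlation. All three points stand and limit the claim.

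Finally, comparisons with A should not be demoted. The aim and objective 1 depend on them.

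**Conclusion.** The concern holds in this limited form. The sample size is justified for control versus intervention, the hypothesis is C–B and C–D, and the four-workplace analyses do not single these out. For BMI at 1 kg/m² and SD 3.77, power is about 51% per contrast and 34% for both, not 80%; the detectable difference is 1.41 kg/m². Part of this comes from dividing a two-group total among four workplaces. For salt, power per contrast is about 95% at 2 g and 43% at an assumed 1 g.

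These figures rest on individual-level calculation, two-sided 5% tests, full follow-up, no clustering and the stated SDs used without baseline adjustment. They are optimistic in one respect that no sample size repairs: with one workplace per arm, each contrast is confounded with workplace. That is a separate point, but it limits what C–B and C–D can show.

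**What to change.** 1. State in the protocol and analysis plan that C–B and C–D, each as a difference in change from baseline, are the contrasts that address the study hypothesis, and that for a given outcome it is supported only if both are shown. Requiring both needs no split of the 5% level within that outcome; it does not deal with multiplicity across the several primary outcomes.
2. Say that an overall four-workplace test, or C better than A, does not by itself support the hypothesis.
3. Keep the comparisons with A as the analysis for the aim and objective 1.
4. Restate power or detectable difference for C–B and C–D at 112 per workplace, for BMI and for salt. Give any baseline correlation used as an assumption with a range. Note that with one workplace per arm the figures are optimistic and each contrast is confounded with workplace.

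The cost is wording only, with no change to recruitment. The downside is that the power stated for the hypothesis becomes lower.

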### Study objectives

The key objectives for this study are:

1. To develop long-term workplace complex dietary interventions focused on environmental dietary modification alone or in conjunction with nutrition education in large manufacturing workplace settings and evaluate the impact of these interventions on employees’ dietary behaviour, health status and nutrition knowledge.

2. To investigate employees’ food choice motives in a working environment.

3. To conduct a process evaluation that will include all key stakeholders to define critical elements in the success or failure of the complex dietary interventions.

4. To evaluate and compare the alternative interventions in terms of their costs and consequences.

## Methods/design

The complex intervention design has been developed and will be evaluated using the Medical Research Council’s framework [6]. The four phases of the framework are development, feasibility and piloting, evaluation, and implementation; these are illustrated in Figure 1.

**Figure 1 F1:**
[figure not shown]
**Medical Research Council’s framework: 'Developing and evaluating complex interventions: new guidance’.** The complex intervention design has been developed and will be evaluated using this framework.

### Development

This phase focuses on (1) identifying the evidence base, (2) identifying and developing a theoretical understanding, and (3) modelling the process and outcomes for the complex intervention.

#### Identifying the evidence base

We conducted a systematic review on the impact of workplace dietary modification interventions alone or in combination with nutrition education [14]. The review was guided by the PRISMA statement [19]. Although there was evidence that some interventions can moderately increase fruit and vegetable consumption, results show that uncertainty remains regarding the long-term effects on dietary behaviour, health status and economic cost. The systematic review findings informed the intervention design.

#### Identifying and developing theory

This intervention design will comply with a soft paternalistic 'nudge’ theoretical perspective [16]. The intervention will create positive reinforcement with indirect suggestions for healthy food choices to try to improve dietary behaviour with unforced compliance. Environmental engineering approaches will be guided by choice architecture that will include food modification, relocation of healthy food options and price discounts.

#### Modelling process and outcomes

This behavioural complex intervention design is guided by the detailed principles and recommendations of the NICE guidelines [1]. The study focuses on two potential methods to improve long-term dietary behaviour in the workplace including environmental dietary modification and nutrition education. Both methods will be measured independently and collectively in purposively selected workplaces. Workplace A (the control) will continue to follow usual practice. No changes will be implemented. Workplace B will receive nutrition education. Workplace C will receive nutrition education and environmental dietary modification. Workplace D will receive environmental dietary modification alone. The intervention design has been developed by the research team (nutritionists, dieticians, public health and health promotion researchers), catering stakeholders in Ireland (representatives of the Catering Managers Association of Ireland), workplace stakeholders (catering managers, human resources managers, occupational health managers) and the target population, that is manufacturing employees. Figure 2 illustrates the trial design.

**Figure 2 F2:**
[figure not shown]
Food Choice at Work trial design.

Study outcomes will assess the effect of the intervention on dietary behaviours and improvements in diet-related disease risk. Primary outcomes will include changes in dietary behaviour and health status. Analysis of multiple 24-hour dietary recalls, food frequency questionnaires, food sales data and food purchasing patterns will indicate changes in dietary behaviour. Changes in body mass index (BMI), waist circumference, resting blood pressure and urinary electrolytes, including sodium and potassium (24-hr urine collections and random urine samples) will highlight improved health status outcomes. Secondary outcomes will determine food motives [20] and eating behaviours [21], changes in nutrition knowledge [22] and economic cost outcomes. A cost-effectiveness economic evaluation will be conducted and absenteeism trends will be recorded during the study period.

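### Two whole outcome domains are primary, and the full 5% level is claimed for BMI and again for salt at two follow-ups with three intervention workplaces, so no single variable, time point or contrast decides the trial; nutrition knowledge also has two roles.

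*Protocol article*

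**What the plan says.** All references are to the protocol article.

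- **Modelling process and outcomes** (outcomes paragraph after Figure 2): "Primary outcomes will include changes in dietary behaviour and health status". The first domain is filled in as follows: "Analysis of multiple 24-hour dietary recalls, food frequency questionnaires, food sales data and food purchasing patterns will indicate changes in dietary behaviour". The second is filled in with "Changes in body mass index (BMI), waist circumference, resting blood pressure and urinary electrolytes, including sodium and potassium".
- **Same paragraph, secondary outcomes:** "Secondary outcomes will determine food motives [20] and eating behaviours [21], changes in nutrition knowledge [22] and economic cost outcomes".
- **Statistical analysis:** "Primary analysis will examine the effects of the interventions by measuring changes in dietary behaviour, health status outcomes and nutrition knowledge". It adds: "Mean levels of macronutrients, fibre, salt, fruit and vegetable intake in workplaces A, B, C and D will be compared".
- **Determination of sample size:** 80% power at the 5% level for a 1 kg/m² BMI difference "between the control and intervention groups at follow-up session after 7 to 9 and 13 to 16 months". The same power and level are then claimed for salt, "at follow-up periods of 7 to 9 and 13 to 16 months".
- **Modelling process and outcomes:** workplace A is the control. B receives education, C receives education plus environmental modification, and D receives environmental modification alone.
- **Study hypothesis:** the combined intervention (C) is better than either component alone (B or D). The sample-size section, by contrast, speaks of control against intervention.

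**The concern.** A domain is not an endpoint. Several measures stand under each of the two primary domains, and the dietary sources each yield several nutrients. The sample-size section does single out two variables, BMI and salt. It does not say whether success needs one or both, which follow-up decides, or which of the three intervention workplaces must differ from control. It spends the full 5% on each variable.

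The hypothesis points to other contrasts (C with B, C with D), so the deciding comparison is open as well. The two roles given to nutrition knowledge blur the line between primary and secondary further.

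At stake is whether the 5% in the sample-size section describes the trial's error rate. As written, a nominally significant result on one variable, at one follow-up, in one workplace could be reported as the primary finding.

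**Working it through.** **1. The plan's own figure.** For BMI with a difference of 1 and SD 3.77, two-sided 5% and 80% power, n per group = 2 × 3.77² × (1.960 + 0.842)² / 1² = 223.1, rounded up to 224. Two groups give 448, the stated total. The figure therefore belongs to one two-group comparison of one variable at one time. It contains no allowance for a second variable, a second follow-up or three intervention workplaces.

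**2. Count of comparisons on the two sized variables.** 2 variables × 2 follow-ups × 3 intervention workplaces against control = 12.

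**3. Chance of at least one false positive, each test at 5%, no true effect.**

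- *Independent tests:* 1 − 0.95^12 = 46.0%.
- *Correlated tests:* simulation with 200,000 multivariate-normal draws. The three contrasts have correlation 0.5 because they share the control with equal group sizes. The other correlations are assumptions, as the document gives none.

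| Correlation between follow-ups | Correlation between outcomes | At least one false positive |
|---|---|---|
| 0 | 0 | 41.5% |
| 0.5 | 0.5 | 36.5% |
| 0.9 | 0 | 31.6% |
| 0.9 | 0.5 | 29.4% |

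For comparison, one variable at one follow-up with three contrasts gives 12.5%. One variable, one follow-up and one contrast gives 5%.

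**4. Splitting 5% over the two endpoints alone is not enough.** At 2.5% per endpoint with three contrasts each, six independent tests give 1 − 0.975^6 = 14.1%. With the shared control and an outcome correlation of 0 to 0.5, simulation gives about 12% to 13%.

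**5. Power at 112 per workplace, one workplace against control (two-sample t test, two-sided).** The non-centrality is difference / (SD × √(2/112)).

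- Salt: 2 / (4.2 × 0.1336) = 3.56.
- BMI: 1 / (3.77 × 0.1336) = 1.98.
- BMI as change with an assumed baseline-to-follow-up correlation r = 0.8: SD = 3.77 × √(2 × 0.2) = 2.38, giving 3.14.

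| Level | Salt | BMI, SD 3.77 | BMI change, r = 0.8 assumed |
|---|---|---|---|
| 5% | 94% | 51% | 88% |
| 2.5% | 90% | 39% | 81% |
| 0.83% (first Holm step over six tests) | 82% | 25% | 68% |

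**6. Nutrition knowledge.** The outcomes paragraph classes it as secondary. The statistical analysis section names it beside exactly the two primary domains as an object of the primary analysis. No arithmetic applies; the two sections give it different roles.

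**The case against.** **The 5% per test is not written down.** It appears only in the sample-size section, and an unseen SAP could hold an adjustment. This stands as far as the error rates go: they are conditional on an inference, and the absence of an adjustment is not the finding. It does not rescue the endpoint. The article itself makes two domains primary and sizes the trial on two variables at two times, so a SAP would have to choose the endpoint, not merely implement it.

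**The 12 pairwise tests are a construction.** The analysis section plans a repeated measures ANOVA across the four workplaces and a mixed effects model. One omnibus test for each of the two sized variables would give at most 1 − 0.95² = 9.75%. That is fair. But the sample-size section frames its claim as control against intervention at each follow-up, and an omnibus test does not say which intervention worked.

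**A reader might infer that a false positive primary result is more likely than not.** Counting eight listed sources and measures (four dietary, four health) gives 48 tests: 91.5% if independent, 65% to 88% with assumed correlations. The documents do not support that as the headline. They specify no such set of tests, for example none for food sales. On the two sized variables the figure stays below even odds.

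**Primary analysis need not mean primary outcome.** It may mean the main-effects analysis, since the subgroup section uses secondary analysis for external factors and subgroups. This reading is plausible, so the conflict is one of role and wording and does not drive the error rate. It still needs reconciling.

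**EQ-5D is called primary in the economic evaluation.** That applies only within that evaluation and is not counted here.

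**Conclusion.** The point holds in this form: the protocol article fixes its primary endpoint badly. It names two open-ended domains and claims the full 5% for BMI and again for salt at two follow-ups. It does not say which variable, follow-up or contrast decides, and it gives nutrition knowledge two roles.

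For the two sized variables, the chance of at least one false positive is about 29% to 42%, or 46% under independence. This assumes 12 comparisons each at 5%, no true effect, the stated correlation ranges, and independent employees. It is higher if every listed measure counts as primary. The figures are taken before any effect of clustering. The plan puts the primary unit of analysis at workplace level with one workplace per arm, so they do not give the trial's actual error rate; they show what the multiplicity alone would do.

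**What to change.** Amend three places in the protocol article.

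1. **Outcomes paragraph (Modelling process and outcomes):** limit the primary endpoints to BMI and dietary salt, the two the trial was sized on, at one named follow-up. Make every other measure secondary, without a confirmatory claim.
2. **Determination of sample size:** name the deciding contrast, or an ordered set of contrasts, consistent with the study hypothesis (C against B and C against D). State the success rule, and restate power for that contrast. Control 5% over endpoints and contrasts together, for example by Holm or a fixed sequence over all of them. Test the other follow-up only after success at the first. Which follow-up comes first is the sponsor's choice: the long-term follow-up section stresses 16 months for sustainability, while the intervention ends at 9 months.
3. **Statistical analysis:** take nutrition knowledge out of the primary analysis, so that it is secondary throughout.

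**Cost.** The edits need no new data; the price is power per test. With one contrast and 2.5% per endpoint at 112 per workplace, salt falls from 94% to 90% and BMI from 51% to 39% on the plan's SD (88% to 81% if BMI is analysed as change with the assumed r = 0.8). Holm over two endpoints and three contrasts starts at 0.05/6 = 0.83%, giving 82% for salt and 25% for BMI (68% with r = 0.8). A single contrast or a fixed sequence is therefore cheaper. BMI has only 51% power in a one-workplace comparison even without adjustment, so the sample-size statement needs recomputing for the chosen contrast in any case.
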